## Abstract

**Background:**

A gene-based estimate of lung cancer risk in smokers has been shown to act as a smoking cessation motivator in hospital recruited subjects. The objective of this trial is to determine if this motivator is as effective in subjects recruited from an NHS primary care unit.

**Method/Design:**

Subjects will be recruited by mailings using smoking entries on the GP electronic data-base (total practice population = 32,048) to identify smokers who may want to quit. Smoking cessation clinics based on medical centre premises will run for eight weeks. Clinics will be randomised to have the gene-based test for estimation of lung cancer risk or to act as controls groups. The primary endpoint will be smoking cessation at eight weeks and six months. Secondary outcomes will include ranking of the gene-based test with other smoking cessation motivators.

**Discussion:**

The results will inform as to whether the gene-based test is both effective as motivator and acceptable to subjects recruited from primary care.

**Trial registration:**

Registered with Clinical Trials.gov, Registration number: NCT01176383.

## Background

Gene testing in primary care is no longer limited by their exorbitant cost. The prices of genetic tests are dropping faster than Moore’s law for computing costs [1]. This leads the focus to shift from cost of genetic testing to the clinical value of individual gene tests. The recent development of gene-based tests that predicts the risk of lung cancer in smokers is an important example [2].

Despite the well accepted 10-15% probability of lung cancer in smokers, 50% of smokers do not believe they are at significantly increased risk [3]. However, over 80% of smokers would like to know their personal risk of lung cancer [4]. There is a plausible three way link between biomarkers for chronic obstructive pulmonary disease (COPD), a set of 20 single nucleotide polymorphisms (SNPs) associated with cancer risk and lung cancer [5-8] (Figure 1). Research has shown a strong association between a high lung cancer susceptibility score derived from family history of cancer, the 20 SNPs, COPD history (Auckland formula) and the development of lung cancers whereas healthy smokers matched for age, gender and lifetime smoking habits had a relatively low score (n = 446 lung cancer subjects, 484 healthy current smokers). The odds ratio for lung cancer risk varied from 0.2-3.2 depending on the genetic risk (p < 0.001) [9,10]. The accuracy of the Auckland formula in estimating lung cancer risk for a score of >4 was: sensitivity 90%, specificity 45% (Figure 1 which also includes scores for 52 subjects who developed cancer from a six year prospective study of 1212 smokers and ex-smokers). The score for prediction of non-cancer was conducted with a follow up of just six years. It means that 45% of non-cancer subjects have a low cancer score and 55% have some degree of increased score. The 55% with increased scores have simply not been followed up long enough for lung cancers to develop yet. Notwithstanding this limitation there is now a 20 SNP gene test for prediction of lung cancer in smokers under the trade name *Respiragene*.

**Figure 1 F1:**
[figure not shown]
**Research that established the respiragene test.** Distribution of the Respiragene score in a cross-sectional study of 484 control smokers (blue) and 446 with lung cancer (red) (Total = 930) and from the prospective study of 52 lung cancer cases (green). Reference [8].

Two case-control studies showed a 5-10% increase in cessation with a single gene test of small effect [11,12]. A small smoking cessation pilot study using spirometry results and explanations using the Fletcher-Peto diagram to explain risk demonstrated that patients find this is an acceptable method and the quit rate at 12 months was 27% [13]. In a randomised control trial patients were given either a full explanation of the results of spirometry testing, including an estimation of lung age or just their forced expiratory volume in the first second (FEV1), without explanation (control group). The group of patients who were given the full explanation had a 7.2% higher quit rate than the control group [14]. Data from a hospital outpatient cohort in Auckland suggest a larger increase in quit rate with *Respiragene* test and the Auckland formula (Table 1). Subjects, who were current smokers in the pre-contemplative and contemplative stage, were randomised into either the test group or control group and only the test group had the *Respiragene test*. Counselling and follow-up was done by telephone. Using Auckland formula to incorporate the results of the *Respiragene* test, clinical data and family history a score ranging 1-12 with associated risk level (moderate risk, high risk, very high risk) was calculated and explained to test subjects. Neither group were involved in any formal smoking cessation programme. Indeed, of the 13 subjects that had managed to stop smoking, (28% of the gene-tested group), 48% quit without any medical assistance and only 52% had nicotine replacement therapy [15,16]. When compared with previous studies using telephone counselling alone [17] (Figure 2), there is a 20-25% improvement in smoking cessation with the *Respiragene* test (Table 1). The improvement in intention to quit increases from 56% before testing to 67% in smokers with an average smokers risk of lung cancer or 89% in smokers with a high risk of lung cancer [18].

**Table 1 T1:** Respiragene study in Auckland NZ (n = 43)

	**Cancer susceptibility scale (compared with normal lifetime risk)**	**Cancer susceptibility score**	**Estimated lifetime risk of lung cancer**	**Initial intention to quit**	**Proportion that stopped smoking at 2-4 weeks**	**Proportion still not smoking at 6 months**
Expected result for telephone counselling (Figure 2)	-	-	15%	41%	10-20%	9-12%
Telephone counselling + Respiragene test	1-2.3 (10-35% risk) 2.3-6.7 (35-65% risk) 6.7-8 (65%-80% risk)	27 had average risk score	15%	67%	8/27 (30%)	8 (30%)
		16 had high or very high risk score	30-50% (4-10 times average risk)	89%	10/16 (63%)	6 (37.5%)

Smoking cessation after Respiragene testing and estimation of lung cancer risk with telephone counselling in a small pilot study in Auckland NZ (n = 43) compared with expected quit rate.

**Figure 2 F2:**
[figure not shown]
**Efficacy of the variety of smoking cessation strategies.** Percent increase of success for six months over unaided attempts for each type of quitting (chart from West & Shiffman based on Cochrane review data). Totally unaided smoking cessation has a 3-6% success rate. Therefore telephone support (Table 1) increases success rate by 6% = 9-12% quit rate.

A large hospital trial using *Respiragene* for calculating lung cancer susceptibility is currently underway in the USA [19], but there are no planned UK investigations. This study fills that gap and uses the NHS framework for smoking cessation. Other studies have taken place looking at how lung functioning testing in COPD might motivate smokers to quit, suggesting that it is feasible to conduct this sort of study [13,14,20]. This protocol describes a trial to evaluate a gene-based risk test (using genetic and clinical data) as a smoking cessation motivator, in smokers wishing to participate in an NHS primary care smoking cessation clinic (in the action stage of change), alongside the usual counselling and prescribing protocol. It will differ from previous studies using gene testing as a motivator, however, in that the NHS primary care counselling and prescribing protocol will include several other motivators (CO breath testing, saliva cotinine testing and intensive counselling) whereas the Auckland trial, using the same gene test, had none of these. Also, the method of recruitment will differ in that primary care subjects will, of necessity, be different from the Auckland hospital outpatient cohort [15,16].

### Research question

Can the *Respiragene* test combined with an estimation of lung cancer susceptibility be used to increase the uptake, adherence to and success rate in an established smoking cessation programme in subjects who want to quit in a National Health Service, United Kingdom (NHS UK) setting?

### Hypothesis

Genetic testing and estimation of lung cancer susceptibility should increase “smoking cessation outcomes” at six months to >30% (or 1.5-2 fold greater than usual care) irrespective of the risk scores assigned to subjects [11].

## Method/Design

This protocol has been approved by Surrey Research Ethics Committee at the Royal Surrey County Hospital, Guildford, Surrey, UK.

### 1/Recruitment

#### Focus groups

A number of focus groups of different aged smokers will be held to enable them to contribute to the design of the study

### 2/ Recruitment

Subjects will be recruited from a large general practice in Surrey (practice population= > 30,000). Smokers aged 20-70 years will be identified from the practice records and contacted by post by their GP. Patients who reply stating that they wish to stop smoking will be randomised (stratified randomisation to ensure equivalent age and gender mix) to two clinics (Figure 3) only one of which will include the gene-based test. Previous trials of genetic testing in association with smoking cessation achieved 83-100% of participants opting for the test depending on the method of recruitment [8,21]. There will be two mailings with SAEs for recruitment with the aim of recruiting at least 30 subjects per clinic (see Power calculations under heading “statistics”). In the first letter the patient’s GP asks the patient to give permission for the researcher to contact him/her to ask about taking part in smoking cessation research (with possible genetic risk testing) and encloses fact sheet 1 and a stamped addressed envelope (SAE) for reply.

**Figure 3 F3:**
[figure not shown]
Consort 2010 flow diagram for GeTTS recruitment.

Mailing 2. The principal investigator mails patient with Letter 2 to ask him/her if they would like to attend an 8-week smoking cessation clinic and asks if they would be willing to have a test for genetic susceptibility to development of lung cancer and encloses SAE for reply.

Mailing 3. The principal investigator mails Group B subjects and Group A test-concordant subjects to confirm dates of the smoking cessation sessions and full patient information leaflet and consent form enclosed. The information sheet will be slightly different for group A and B. Non-test concordant subjects within group A will be invited to attend the practice nurse for smoking cessation.

### 3/Inclusion and exclusion criteria

i. **Inclusion criteria:** Aged 20-70 years, smoking more than 10 cigarettes daily.

ii. **Exclusion criteria:** Aged under 20 years or over 70 years, smoking less than 10 cigarettes daily, history of major depression and other psychiatric conditions, dementias and serious or terminal illness (cancers etc.). Patients on warfarin would be excluded due to interactions between warfarin and varenicline as varenicline will be used as the modern treatment of choice for smoking cessation. Patients who smoke less than 10 cigarettes/day and patients who did not wish to have a genetic test or do not wish to take part in a research study will be referred to the practice nurse for smoking cessation.

•This is followed by seven more weekly sessions and a follow-up session at six months (Figure 4). Uptake and adherence to smoking cessation will be monitored by weekly carbon monoxide exhalation measurements (breath test). The principal investigator will be involved in clinic A administering the gene-based test and determining if subjects have COPD from practice records and history in session 1. Participants who are heavy smokers, have a smokers cough and use a salbutamol inhaler can be judged to have COPD even if this is not entered in their GP records (all Group A & B subjects will have spirometry at their 6-month follow-up). Subsequently the principal investigator will report back to clinic A patients with estimated lung cancer risks (session 3). To ensure balance in the control clinic the principal investigator will also attend Clinic B sessions 2 and 3 (see Figure 5 flow charts).

•At the eight week clinic and the 6-month follow-up clinic smoking cessation status and carbon monoxide breath test score will be recorded and a feedback questionnaire used to assess efficacy of various components will be administered.

Mailing 4. Telephone calls followed by letters to patients with invitation to 6-month follow-up session with NHS Smoking Cessation Practitioners and the principal investigator when cessation rate will be assessed and verified by repeating the carbon monoxide breath and salivary cotinine tests.

– for further details see Figure 5: flow charts

**Figure 4 F4:**
[figure not shown]
Timeline of project.

**Figure 5 F5:**
[figure not shown]
**Flow chart for the duration of the trial. a**. Flow chart of project from start to week 12. **b**. Flow chart of project to week 36.

We anticipate good attendance at the eight week free smoking cessation clinic, as would be expected if it were a regular NHS smoking cessation clinic but the attendance at the 6-month follow-up clinic may be more challenging. We consider this attendance essential and as attendance will take up an evening of their time, study participants should be paid for their travel expenses (£20) and will receive up to three reminders. Group B subjects attending at the 6-month follow up who have been unable to quit will be offered the gene-based test at this stage.

### Technique for taking the respiragene test

The test requires a Buccal swab and the subjects should not eat or drink within 15 minutes prior to supplying a sample (if has eaten or taken a drink within 15 minutes then rinse mouth with tap water). The nurse taking the sample should wear latex or plastic gloves and take care to avoid contact with the buccal swab collection tip to avoid DNA (deoxyribonucleic acid) contamination. Then:

1. Open buccal swab package at the handle end and carefully remove the swab.

2. Holding handle end of swab stick, scrape the collection tip firmly against the inside of the cheek 5-6 times (about 10 seconds), being careful not to press the plunger that ejects the tip.

3. After taking the sample, eject the swab tip into a labelled 2 ml microcentrifuge tube by firmly pressing the plunger at the end of the handle.

4. Complete and affix the sample tube label onto the microtube. The sample label requires the anonymised trial code for the subject.

### Storage of the respiragene test

After sample collection, tips can be kept at room temperature if they are posted immediately. If storage is necessary, freeze the tubes containing the tips at -20°C.

### Packaging instructions for return of samples to Lab21 Ltd

1. Place absorbent material around the tube and then place tube in the plastic bag provided with the kit. Seal the plastic back as per the instructions on the bag

2. Place the plastic bag containing the sample tube into the shipping box.

3. Seal the box with the security seal supplied.

4. Using the Freepost service provided, send the samples to: Lab 21, [name].

Patients will be asked to sign a disclaimer form that explains clearly that this test can only give an estimation of cancer risk and is a test that is still under development (one copy of form for investigators and one for patient).

### Interpretation of result of respiragene test

Lung cancer susceptibility is calculated using the Respiragene test Auckland formula [7]:

Lung cancer score = (number of susceptible genotypes) - (number of protective genotypes) + 3 (for positive family history) + 4 (for past history of COPD) + 4 (for age > 60 years old).

The laboratory reports include the scores with an explanation of how the scores relate to a risk category (see Table 1). When the subject is aged <60 years, the report will also include the score and risk category that would apply if the subject is still a smoker at age 60 years or over.

### Follow-up questionnaires

The questionnaires will be slightly different for groups A (questionnaire 2a) and B (questionnaire 2b) as only 2a will contain a direct reference to the gene-based test. Patients who fail to attend at eight weeks and six months will be contacted by telephone to remind them to complete their questionnaires and hand them in to the practice manager. They are designed to determine which subjects have quit smoking or cut down and which subjects who have failed to quit still plan to do so. There is a section that asks about general motivators and components of the smoking cessation programme. The subjects will be asked to score these motivators and smoking cessation aids for their efficacy in helping them to quit. The questions in this section are almost identical to a validated questionnaire [24]. There are also further questions on whether the subject would recommend the *Respiragene* test to a relative or friend and an open ended question for subjects to add their own comments about the concept of a test that predicts susceptibility to lung cancer in a smoker.

### Data quality assurance

The study has been designed and will be reported in accordance with CONSORT (Consolidated Statement of Reporting Trials) [25]. Data will be controlled in accordance with data protection legislation, institutional protocols of Sussex NHS Research Consortium, and NHS policies for research and information governance for ensuring patient confidentiality [26]. Data will be analysed in SPSS (Statistical Package for Social Sciences) version 15 using an intention to treat approach.

### Outcome measures

#### Primary endpoint

Comparison of smoking cessation rates (7 day point abstinence and continuous abstinence) in Clinic A and Clinic B at 8 weeks and six months.

#### Secondary endpoints

A. Personal data:

1. Number of smokers still smoking who state that they still plan to stop.

2. Daily cigarette consumption of those still smoking.

3. Mean scores for ranking of smoking cessation aids (gene-based test - Clinic A only, salivary cotinine, lung cancer facts - controls in Clinic B only and general counselling from NHS smoking counsellors).

B. Analyse questions about whether subjects would recommend the test to a member of family or a friend.

C. Analyse last (open ended) question using qualitative research methodology.

### Statistics

#### Primary end point

The difference between smoking cessation between Clinic A and Clinic B will be estimated from the four week and six month follow up for the primary endpoint (smoking status confirmed by carbon monoxide breathalyser and salivary cotinine tests). If there is the expected higher rate of smoking cessation for Clinic A compared with Clinic B, statistical significance will be demonstrated by the χ^2^ test.

Since there are, as yet, no case-control studies that compare quit rate following the gene-based test versus quit rate without the test, the expected difference in quit rate between Clinic A and Clinic B is difficult to estimate. Two case-control studies showing only a 5-10% increase in smoking cessation involved just a single gene of small effect [11,12]. In a randomised control trial patients were given either a full explanation of the results of spirometry testing, including an estimation of lung age or just the FEV1, without explanation (control group). The group of patients who were given the full explanation had a 7.2% higher quit rate than the control group. However, data from Auckland suggest a larger uplift of quit rate with *Respiragene.* This can be explained by the superior predictive power of a 20-gene test combined with clinical history (personal history of COPD and family history of lung cancer) to give a rather more impressive estimate of cancer risk than anything previously available.

The adequacy of sample size was tested using data from smoking cessation trials that showed:

•30-40% smoking cessation at 6-months with similar protocols [27,28].

•A 48% quit rate at 2-4 weeks in subjects with high and very high lung cancer risk scores but this difference shrinks to 27% at 6 months.

•Data from Young et al [15,18] (independently verified by McBride et al [11]) that even being given an average score for lung cancer susceptibility increases smoking cessation by approximately 10%.

Therefore, with a minimum sample sizes of 30 per group the following calculations based on these estimated quit rates apply (Table 2). Statistical power of 87.1% is generally acceptable for publication (for alpha error of 5% - i.e. 5% probability of incorrectly rejecting the null hypothesis that there is no difference in the percentage values). For further detailed statistical analysis, refer to Additional file 1.

**Table 2 T2:** Summary of values from which the power of the study are estimated

		**Control group expected quit rate as %ge**	** *Respiragene * ****group expected quit rate as %ge**	**χ**^**2 **^**calculated from four-some table**	**P value based on χ**^**2**^	**Power calculations***
8 weeks	Sample size 30/30*	70%	94%	5.9	<0.05	79.3%
	Sample size 60/60*			11.7	<0.01	96.9%
6 months	Sample size 30/30**	35%	52%	1.7	NS	36.5%
	Sample size 60/60**			6.2	<0.05	87.1%

*Telephone (alone) quit rate (see Table 1) assumed to be 20%.

**Telephone (alone) quit rate (see Table 1) assumed to be 10-15%.

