### What we might find

We aim to recruit a minimum of 60 subjects to randomise 30 into group A (test group) and 30 into Group B (control group). The normal experience in NHS smoking cessation clinics is a drop-out rate of 40-50% [30-32]. We need, therefore, to attempt to recruit about 120 subjects in order to get a statistically significant result, based on the assumptions in our power calculations. We may, however, have underestimated the 6-month quit rate using the NHS local stop smoking guidelines [22] which typically involves a multi-interventional programme which includes combinations of varenicline prescriptions, breath carbon monoxide monitoring and intensive counselling giving a quit rate of 70-80% at 6-weeks.There are however no Surrey data for 6-month quit rate which we assume, on the basis of similar smoking cessation data to be about half the 6-week figure [33] ≅ 35%.

An unknown and unpredictable factor, that could skew results significantly, is the possibility that our multi-interventional approach could help to reinforce the health risk message equally for subjects in both groups. Also, the Auckland study design involved recruitment of precontemplative-contemplative smokers from a hospital outpatient setting, compared to this study that will involve primary care subjects who have volunteered to participate in a smoking cessation programme (ie smokers in the action stage of quitting). This population, therefore, could be sufficiently different to give unexpected results. However, the results of this trial will inform as to the acceptability of this approach as well as its effectiveness.

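### The primary χ² test is worded as conditional on Clinic A having the higher observed quit rate, with no test given for the opposite result and sidedness left unstated

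*Protocol article*

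**What the plan says.** All references are to the protocol article.

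- **Statistics, Primary end point** first commits to estimation, without any condition on direction: "The difference between smoking cessation between Clinic A and Clinic B will be estimated from the four week and six month follow up". The next sentence gives the test: "If there is the expected higher rate of smoking cessation for Clinic A compared with Clinic B, statistical significance will be demonstrated by the χ^2^". Nothing says what is done if Clinic A's rate is equal or lower.
- The same section explains its 5% alpha as "5% probability of incorrectly rejecting the null hypothesis that there is no difference in the percentage values". It does not say whether the test is one- or two-sided.
- **Outcome measures, Primary endpoint** has no direction: "Comparison of smoking cessation rates (7 day point abstinence and continuous abstinence) in Clinic A and Clinic B at 8 weeks and six months".
- **Hypothesis** does have a direction: "Genetic testing and estimation of lung cancer susceptibility should increase “smoking cessation outcomes” at six months to >30"%.
- **Secondary outcome measures** assigns the χ² test to most secondary endpoints with no condition on which clinic does better.
- **Table 2** gives χ², a P value based on χ², and power for 30 and 60 per group. Its 30-per-group rows are "70% 94% 5.9 <0.05 79.3"% at 8 weeks and "35% 52% 1.7 NS 36.5"% at 6 months.

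**The concern.** Whether a test is made should not depend on the result it is meant to judge. Here the condition is the observed direction of the primary comparison. A null of no difference combined with an undirected endpoint leads a reader to expect a test that can reject either way. The test sentence provides for one way only.

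What is at stake is the decision when Clinic A quits less often than Clinic B. Under an ordinary two-sided χ² test such a difference could be declared significant. Under the sentence as written no test is specified, so the choice would be made after the data are seen. The protocol allows for surprises: comparing its recruits with the Auckland cohort, it says "This population, therefore, could be sufficiently different to give unexpected results". An analysis fixed in advance for either direction is what makes a surprising result usable.

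**Working it through.** **Inputs.** Quit rates of 70% v 94% (8 weeks) and 35% v 52% (6 months), 30 or 60 per group, and the stated χ², P values and powers are from Table 2. Alpha of 5% is from Statistics, Primary end point. The calculations use the uncorrected χ² and treat participants as independent, and they concern one comparison at a time.

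**Step 1: which sidedness does Table 2 use?** With n per group, d the difference and p̄ the mean of the two rates:

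χ² = n·d² / [2·p̄(1 − p̄)]

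power = Φ( [d√n − z√(2p̄(1 − p̄))] / √(pA(1 − pA) + pB(1 − pB)) ), with z = 1.645 one-sided or 1.960 two-sided.

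Worked for 70% v 94%, n = 30:
- p̄ = 0.82, so χ² = 30 × 0.0576 / 0.2952 = 5.85 (stated 5.9).
- One-sided power: (1.3145 − 0.8937)/0.5161 = 0.815, giving 79.3%.
- Two-sided power: (1.3145 − 1.0649)/0.5161 = 0.484, giving 68.6%.

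| Row | χ² stated / computed | Power stated | One-sided 5% | Two-sided 5% |
|---|---|---|---|---|
| 8 weeks, 30/30 | 5.9 / 5.85 | 79.3% | 79.3% | 68.6% |
| 8 weeks, 60/60 | 11.7 / 11.71 | 96.9% | 96.9% | 93.8% |
| 6 months, 30/30 | 1.7 / 1.76 | 36.5% | 37.4% | 26.1% |
| 6 months, 60/60 | 6.2 / 3.53 | 87.1% | 59.4% | 46.7% |

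The first two powers match one-sided exactly and the third to within a point; none of the three matches two-sided. The fourth row matches neither, and its χ² is also wrong for the stated rates. That is a separate error.

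The P column points the other way. Ordinary (two-sided) χ² P values for 5.9 and 6.2 are 0.015 and 0.013, in line with the table's label of below 0.05. Halved for a one-sided test they would be 0.0076 and 0.0064, which one would expect under the below-0.01 label that the table uses for 11.7 (P = 0.0006).

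**Step 2: false-positive rate of the literal rule.** Enumerate every pair of binomial counts with equal true rates, and count a rejection only when A > B and χ² exceeds the cut-off.

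| n per group | True rate, both | Ordinary χ², either direction (3.841) | Literal rule, 3.841 | Literal rule, 2.706 (one-sided 5%) |
|---|---|---|---|---|
| 30 | 35% | 4.77% | 2.38% | 4.68% |
| 30 | 70% | 4.87% | 2.43% | 5.01% |
| 60 | 35% | 5.04% | 2.52% | 5.25% |
| 60 | 70% | 5.25% | 2.62% | 5.07% |

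**Step 3: what is lost in the other direction.** With 35% in both groups, Clinic A is strictly lower in 44.6% (30/30) or 46.2% (60/60) of trials, and the literal rule specifies no test in any of them. The protocol gives no adverse scenario, so two are assumed for illustration:
- 20% in A v 35% in B: the ordinary two-sided χ² would show it in 25.2% (30/30) or 46.4% (60/60) of trials.
- 18% in A v 35% in B, the mirror image of the planned 17-point gain: about 32% or 57%.

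Under the literal rule the figure is 0% in each case, whichever cut-off is used.

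**The case against.** The strongest reply is that the sentence is loose prose, not a decision rule. It says what is expected and names the test; the word *only* is not there. The preceding sentence estimates the difference unconditionally, the endpoint is undirected, and the secondary endpoints get the χ² test with no condition. All this suggests that the authors may have meant to test either way. The article also refers to an additional file for more statistical detail, which is not at hand.

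A second reply is that a null of no difference is quite usual for a one-sided test, and the stated hypothesis is directional. On that view there is no contradiction, only unstated sidedness.

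Both replies have force, and they rule out stronger readings. The word *only* is an inference. The null and the test sentence fit poorly together but do not strictly contradict each other. A reader might infer that an unfavourable result would go unreported, but the difference is to be estimated in any case and CONSORT reporting is promised. A reader might also take the remarks on unexpected results as conceding harm. They say that these subjects may differ from the Auckland cohort, and the specific risk named is that the programme works equally in both groups.

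What stands is that this is the only sentence fixing the primary test. Its condition is the observed result, and the opposite case has no stated test.

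**Conclusion.** The concern holds as a direction-dependent primary test with unsettled sidedness. Followed as written, the rule gives no chance of declaring a lower quit rate in Clinic A significant.

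A reader might infer that the trial's true error rate is 2.5% and that this contradicts the stated 5%. The document does not support that. The 2.4 to 2.6% range needs both the *only if* reading and the two-sided cut-off of 3.841. With the one-sided cut-off that three Table 2 powers imply, the same rule runs at 4.7 to 5.3%. At 3.841 the rule is conservative, so inflation of the type I error is not the complaint either.

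The null-case figures rest on the assumptions listed with the calculation. The adverse-effect figures rest on assumed rates and show only the order of what is forgone.

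**What to change.** Replace the test sentence in Statistics, Primary end point with:

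*The difference in cessation rate (Clinic A minus Clinic B) will be tested by a two-sided χ² test at the 5% level and reported with its 95% confidence interval, whichever clinic has the higher rate.*

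Restate the Table 2 powers on the same two-sided basis: 68.6% and 93.8% at 8 weeks, 26.1% and 46.7% at 6 months (30 and 60 per group). Most of the fall from 87.1% to 46.7% comes from the separate error in that row, since one-sided power there is already only 59.4%.

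The cost is one sentence and a recalculated column, with no extra participants or data. The downsides are that the stated powers become less favourable and that an unfavourable difference must be reported with its P value and interval. If the authors always meant to test in either direction, the new sentence simply says so.

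### The uplift inputs behind Table 2 rest on different baselines, so the planned six-month rate of 52% sits at or just below the low edge of what the pilot supports, and its row must be recomputed

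*Protocol article*

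**What the plan says.** The protocol article (Statistics, Primary end point) lists the inputs used to test the sample size. For high-risk subjects it gives "A 48% quit rate at 2-4 weeks in subjects with high and very high lung cancer risk scores but this difference shrinks to 27% at" six months. For average-risk subjects it says, citing the Auckland data, that "even being given an average score for lung cancer susceptibility increases smoking cessation by approximately 10" per cent. This second input carries no time point, and no other average-risk input is offered.

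Table 1 gives the pilot itself. "27 had average risk score", of whom 8 (30%) had stopped at 2-4 weeks and 8 (30%) at six months. Of the 16 with high or very high scores, 10 (63%) and 6 (37.5%) had stopped. The expected telephone-only rates are 10-20% early and 9-12% at six months.

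Table 2's footnotes assume telephone-only rates of 20% for the 8-week rows and 10-15% for the six-month rows. For six months it plans 35% against 52%. The row marked "Sample size 60/60" prints chi-square 6.2 and power 87.1%, and the text adds "Statistical power of 87.1% is generally acceptable for publication". The Background and the Limitations and assumptions section put the improvement at 20-25%.

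**The concern.** Two uplifts that are combined into one planned rate should be measured against the same comparator at the same time point. The +27 and the +10 appear not to be. Average-risk subjects are 27 of the 43 in the pilot (63%), so their input carries most of the weight in any pooled rate.

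The six-month row is the one whose power figure is offered as adequate. If its rate cannot be traced to one comparator, a reader cannot tell whether the trial was planned for 17 points, for 20-25 points or for something else. The power statement then has no fixed effect size to refer to.

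**Working it through.** **1. Uplift by risk group at six months, from Table 1.** Average risk is 8/27 = 29.6%, high risk is 6/16 = 37.5%, and both together are 14/43 = 32.6%. The planned test-group rate is the 35% control rate plus the pooled uplift.

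| Comparator | Average risk | High risk | Pooled | 35% + pooled |
|---|---|---|---|---|
| 9% | +20.6 | +28.5 | +23.6 | 58.6% |
| 10% | +19.6 | +27.5 | +22.6 | 57.6% |
| 12% | +17.6 | +25.5 | +20.6 | 55.6% |
| 15% | +14.6 | +22.5 | +17.6 | 52.6% |
| 20% (early) | +9.6 | +17.5 | +12.6 | 47.6% |

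The +27 for high risk needs a comparator of 37.5 - 27 = 10.5%. The +10 for average risk needs about 20%. No single row gives both. The early inputs show the same split: 62.5 - 48 = 14.5% for high risk, against about 20% for average risk.

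**2. How the 52% may have arisen.** Weighting by the pilot's 27:16 split:
- Six months: (27×10 + 16×27)/43 = 16.3, so 35 + 16.3 = 51.3%. With +27.5 for high risk it is 51.5%, which rounds to the printed 52%.
- 8 weeks: (27×10 + 16×48)/43 = 24.1, so 70 + 24.1 = 94.1%. Table 2 prints 94%.

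The near match at both time points suggests that +10 was used at both. The weighting is an inference.

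**3. Against the stated improvement.** Over 9-12% the pooled uplift is 20.6-23.6 points, inside the 20-25 stated in the text. Table 2 uses 52 - 35 = 17.

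**4. The six-month row.** Alpha is given as "for alpha error of 5% - i.e. 5% probability of incorrectly rejecting the null hypothesis", with no statement of one or two sides, and the test is chi-square ("statistical significance will be demonstrated by the χ^2^ test"). With n per group, difference d and mean proportion p̄:
- chi-square = n·d²/[2p̄(1-p̄)]
- power = Φ{[d√n - z√(2p̄(1-p̄))]/√(p1(1-p1) + p2(1-p2))}

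Reproducing the printed power first: three of the four cells come out, or nearly so, with a one-sided 5% test. They are 79.3% (printed 79.3%), 96.9% (96.9%) and 37.4% (36.5%). The fourth does not. For 35% against 52% at 60 per group:
- chi-square = 60×0.17²/(2×0.435×0.565) = 3.53, printed 6.2
- power = 46.7% two-sided and 59.4% one-sided, printed 87.1%

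A check needs only the table. Doubling n doubles this chi-square, as it does at 8 weeks (5.9 to 11.7). At six months 1.7 should become about 3.4.

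A chi-square of 6.2 corresponds to a test-group rate of about 57.7%, close to the 10% comparator row. One-sided power of 87.1% corresponds to 60.0%. Neither goes with 52%.

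Power at 60 per group for the rates in step 1:

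| Test-group rate | Chi-square | Two-sided | One-sided |
|---|---|---|---|
| 52.6% | 3.78 | 49.3% | 61.9% |
| 55.6% | 5.14 | 62.3% | 73.7% |
| 57.6% | 6.16 | 70.4% | 80.5% |
| 58.6% | 6.71 | 74.2% | 83.5% |

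**The case against.** The average-risk bullet names no time point. Read as a 2-4 week figure against 20%, it agrees with Table 1 (29.6 - 20 = 9.6). The 27:16 weighting is reconstructed, and the article refers to Additional file 1 for the detail. The bullet cites published Auckland reports, which may use a different comparator from the external expected rate in Table 1. A figure of 8/27 has a 95% Wilson interval of about 16-48%, so +10 over any stated comparator is compatible with it. A lower input is also a reasonable choice for a population that the article itself expects may respond differently. All of this stands, and it limits what can be claimed.

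Three stronger readings are tempting and are not supported:
- **That 52% cannot come from the pilot.** At the 15% end of Table 2's own footnote the pooled pilot gives 52.6%.
- **That the correct rate is 57%.** That follows from choosing 10.5%, the middle of 9-12%. Other comparators within the article's two ranges give anything from 52.6% to 58.6%.
- **That the claimed independent verification is contradicted.** The Background says "Two case-control studies showed a 5-10% increase in cessation with a single gene test of small effect", and about 10% is the top of that range. Whether the cited study verifies the Auckland figure cannot be judged from this document.

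The objection does not remove the mismatch. The article offers +10 as its only average-risk input to Table 2. Every six-month comparator it states gives at least +14.6, and the adjacent +27 uses about 10.5%.

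**Conclusion.** The point holds as an inconsistency of baselines. The planned 52% (+17) lies at or just below the low edge of what the pilot supports, and it disagrees with the 20-25 points stated in the Background and in Limitations and assumptions.

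The direction is conservative: a low average-risk input reduces the planned effect and does not inflate power. The inflated power is a separate and larger error in the same row. Restating the uplift does not rescue it, because no rate between 52.6% and 58.6% reaches 87.1% at 60 per group, one-sided or two-sided.

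The conclusion rests on the Table 1 counts, on the 35% control rate, and on the inference that +10 was carried to six months. The power figures for 35% against 52% need only Table 2's own rates and the 5% alpha.

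**What to change.** - State one six-month telephone-only comparator, choosing between 9-12% and 10-15%, and use it for both risk groups. Alternatively, keep +10 and say that it is a deliberate discount from the pilot, with the reason.
- Give the time point of the average-risk input and show how the two groups were weighted.
- Reconcile the 17 points in Table 2 with the 20-25 points in the text.
- Recompute the whole six-month row from the resulting rate and state whether the test is one- or two-sided. If 52% is kept, the 60/60 cells become chi-square 3.5 and power about 47% two-sided (59% one-sided). Over the footnote's 10-15% range, two-sided power is about 49-70%.

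The cost is one reworded bullet, one recalculated pair of table cells or row, and matching text where 87.1% is cited. No trial procedure changes. The corrected power may prompt a separate decision on sample size: for 80% two-sided power, 35% against 52% needs 133 per group, and rates of 52.6% to 57.6% need 124 down to 76.
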